### Data Analysis

Quantitative and qualitative analyses will be conducted as described below. Findings from stakeholder engagements, focus groups, interviews, and evaluation surveys will be synthesized to develop the implementation tool kit, with iterative platform refinement largely relying on feedback derived from qualitative data. However, the primary study outcomes and feasibility metrics will rely on quantitative data, as described below.

### Statistical Analysis Plan

Data will be analyzed at the aggregate level. To address aim 1 (usability and potential for sustained use), descriptive statistics will be computed on the SUS and recruitment rates to assess whether feasibility targets are met (ie, SUS score ≥68, 25% client eligibility and recruitment rate). Using data collected from the Peer PLUS user log, we will conduct a general categorical analysis as a proxy for end-user engagement. To assess our primary outcome related to client contact, in the pilot trial, we will compare the number and rate of connections to clients using the platform to PRCs’ documentation of contact with nonparticipating clients to determine whether the target of 20% more contacts with enrolled clients was met. Further, to address aim 2 (evaluating the impact of Peer PLUS on treatment-related outcomes), descriptive statistics will be calculated for the SURE, CAHPS ECHO, and WAI-SR survey measures deployed during the pilot trial, which will demonstrate potential improvement related to recovery, quality of care, and therapeutic alliance, as well as the feasibility of using these measures to evaluate the app in the R33 phase.

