### Setting

The study is being conducted within a mid-sized not-for-profit learning health system in the Midwestern United States. The system serves an area with significant need for SUD support and has a robust network of existing treatment pathways, including the largest behavioral health hospital and medication-assisted treatment (MAT) facilities in the region, and has employed PRCs for more than 8 years. The multidisciplinary study team is based at the health system’s embedded Center for Research and Innovation and has prior experience creating digital solutions to support clients while maintaining health information privacy. The team includes researchers specializing in UCD, human-computer interaction, health technologies, clinical psychology, and addiction recovery, including peer recovery coaching. The PRC participants in the present phase of the study are also employed by this health system and are embedded within its emergency departments, MAT clinic, rural health centers, or mobile overdose response teams. These PRCs focus on providing emotional support and connection to treatment-related and community resources, and undergo relevant trainings such as cardiopulmonary resuscitation (CPR), suicide prevention (QPR; Question, Persuade, Refer), and naloxone administration. The PRC team’s manager has an existing collaborative relationship with the research team and has been involved with the project since its initial proposal and design phases.

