**PRC manager: inclusion criteria**
Employed as a PRC manager or supervisor

**Table 3. T3:** Breakdown of the activities as it relates to the initial timeline.

Months	Activities
0‐3	Prelaunch ethnography
4‐8	Beta testing
9‐12	Platform and tool kit refinement
13‐20	Pilot
21‐22	Platform and tool kit refinement
23‐24	Final analysis and Go/No Go R33

The beta tests and pilot will involve app usage by clients and PRC participants as part of their existing support relationship and in addition to standard care, with PRCs additionally using the platform’s client management system. All client participants will be clients of a PRC who is also enrolled in the study, and each PRC participant may have multiple clients enrolled. Participants will be asked to use the app for asynchronous communication outside of in-person meetings, when possible. The length of participant engagement for a beta test or pilot trial was planned to last up to 3 or 6 months, respectively.

During and immediately after their trial period, participants’ perceptions and experiences will be assessed through periodic deployment of electronic surveys along with posttest engagement. During beta testing, these surveys will be focused primarily on the usability of the platform; during the pilot, clients will be additionally surveyed regarding certain treatment outcomes. Descriptions of survey measures are listed in Textbox 3. Further, after each phase, additional user observations, interviews and/or focus groups, and UCD sessions will be conducted. Feedback from participants throughout all phases, in addition to application usage logs, will be used to iteratively refine the app and contribute to the development of a finalized implementation tool kit at study completion (Table 4). Any updates to software functionality or improvement opportunities identified during the beta testing and pilot phases will be implemented and tested by our development and user experience team until the app is stabilized.

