### Prelaunch Rapid Ethnography

Prior to user testing, we planned to conduct a prelaunch rapid ethnography [52] of up to 4 PRCs to document workflows and process requirements that may be altered with the integration of the platform, including direct interaction with clients, caseload management, resource sharing, and report generation. Through these observations, we sought to understand opportunities for improved productivity and client connection, including day-to-day work that is not quantified in existing workflow documentation. This served as the initial foundation for the development of implementation tool kit components.

Several months prior to beta testing, the study team observed 3 PRCs who represented the different types of coaches within our specific program—maternal, community, and emergency department—over a period of approximately 8 hours each. PRCs were identified by their manager as they represented the different types of coaches. The research team reached out to PRCs to assess their interest in participating and obtained verbal agreement to participate. At the beginning of each observation, the researchers explained the procedure and made sure that any questions they might have were answered. Observations were recorded through detailed written notes with time stamps and descriptions. During these observation sessions, paper-based documents containing resources that may be provided to clients were reviewed and copied in preparation for integration into the Peer PLUS platform. To validate and inform the translation of these ethnographic findings into the development of the platform, we subsequently engaged in follow-up discussions with PRCs and managers to provide clarity regarding our observations in a series of co-design sessions. In particular, we collated resources that were collected during these observations and met with 3 PRCs to discuss how to optimally organize and present them in the mobile app. Once the initial version of the app was finalized, we began recruitment for beta testing.

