### Beta Testing and Pilot Trial

#### Sample Size and Planned Recruitment Rate

We planned to conduct up to 3 incremental beta tests of Peer PLUS, with up to 4 PRCs and up to 4 clients per PRC (n=16 clients) per test. After beta testing is completed, up to 15 PRCs and up to 40 clients will pilot Peer PLUS, which is in line with HCI testing practices [53]. After each test phase, select clients and PRCs will participate in stakeholder engagements to reflect on their experiences. The PRC manager will be involved throughout all phases of the study; in the context of our existing collaborative relationship, the manager has provided design input and serves as an intermediary between the research team and PRCs rather than being enrolled as a consented participant. However, the protocol was written to allow for manager participants (eg, in the case of changes to staffing or location). In total, up to 4 PRC managers, 16 PRCs, and 88 clients may participate across both phases; refer to Table 5.

**Table 5. T5:** Maximum number of participants per study activity.

	Peer PLUS^a^ use	Stakeholder engagements	Surveys		
			WAI-SR^b^	SUS^c^ and/or Custom UX^d^	SURE^e^ and ECHO^f^
Each beta test					
Clients	16	8	—^g^	16	—
PRCs^h^	4	4	—	4	—
PRC managers or supervisors	4	4	—	4	—
Pilot					
Clients	40	8	40	40	40
PRCs	15	15	15	15	—
PRC managers/ or supervisors	4	4	—	4	—

a PLUS: People Leveraging Urgent Support.

b WAI-SR: Working Alliance Inventory.

c SUS: System Usability Scale.

d UX: user experience.

e SURE: Substance Use Recovery Evaluator.

f ECHO: Experience of Care and Health Outcomes.

g Not applicable.

h PRC: peer recovery coach.

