#### Pilot Phase

In the pilot phase, we will seek to enroll PRCs in a more naturalistic manner. As such, the study team will obtain a list of all currently employed PRCs from the manager and contact them to assess interest. Once enrolled, their clients will form the pool of eligible participants. The trust between the PRC and the client is key. Thus, a purely naturalistic recruitment strategy for clients is not feasible, as we wanted to ensure that trust in the program had been developed before approaching newer clients to participate in the study, and we did not want to disrupt the health system’s existing processes for engaging clients in the program. The study team will provide recruitment flyers and training on inclusion and exclusion criteria to PRCs so that they can introduce the study to their clients. If an eligible client expresses interest, the PRC will check “Yes” in the “informed about study” section in the client management system. The study team will run reports to identify which clients have been informed about the study and thus need to be contacted for recruitment. For all recruitment activities, participants may be initially contacted by phone and/or email (and/or Microsoft Teams, in the case of PRCs). Institutional review board (IRB)–approved scripts for emails and calls will be used but may be adapted as necessary for clarity and/or to answer participant questions or concerns.

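### The primary contact ratio is pooled over PRCs, so differences in PRC mix between the groups can bias it in either direction around the 20% target; its metric also needs to be fixed as a rate

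*Protocol article*

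**What the plan says.** The Statistical Analysis Plan section of the protocol article sets the level of analysis in its first sentence: "Data will be analyzed at the aggregate level". For the primary contact outcome, the team will "compare the number and rate of connections to clients using the platform to PRCs’ documentation of contact with nonparticipating clients", and the purpose is "to determine whether the target of 20% more contacts with enrolled clients was met". The section describes no stratification, weighting or adjustment by PRC or by type of PRC.

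Other sections show how clients are spread over PRCs:

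- **Setting:** PRCs are "embedded within its emergency departments, MAT clinic, rural health centers, or mobile overdose response teams".
- **Prelaunch Rapid Ethnography:** the three observed PRCs were people "who represented the different types of coaches within our specific program—maternal, community, and emergency department".
- **Sample Size and Planned Recruitment Rate:** "up to 15 PRCs and up to 40 clients will pilot Peer PLUS".
- **Overview of Study Design:** "each PRC participant may have multiple clients enrolled". No quota per PRC is given for the pilot.
- **Recruitment Methods, Pilot Phase:** "the study team will obtain a list of all currently employed PRCs from the manager and contact them to assess interest". PRCs then introduce the study to their clients, and Textbox 2 makes the PRC's judgment of suitability an inclusion criterion.

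The article does not say whether the nonparticipating clients come only from enrolled PRCs.

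**The concern.** Clients are nested in PRCs, and the contact count partly reflects how the PRC works. The enrolled group will be weighted toward PRCs who took an interest and introduced many clients. The comparison group will be weighted toward the rest. If these PRCs differ in how often they contact any client, the pooled ratio mixes that difference with the effect of the app. The bias can run either way.

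The metric is a second problem. The text names both number and rate and does not say which decides. Total number cannot be compared: at most 40 clients are enrolled, while the Discussion says that PRCs dealt with hundreds of existing and potential clients per month. Number per client depends on time observed, and pilot participation lasts up to 6 months, so it may differ between clients.

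The ratio is a primary outcome and one of the feasibility metrics behind the Go/No-Go step to the R33 phase (Table 3). A ratio displaced by PRC mix could be read as the target met, or could hide a real increase.

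**Working it through.** **The plan's own figure.** The article derives no sample size, power or precision for the contact outcome. The 20% is a target, so there is no calculation to reproduce.

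**Inputs from the article.** Threshold ratio 1.20; at most 15 PRCs and 40 clients, so on average at most 40/15 = 2.7 enrolled clients per PRC. Contact rates, caseloads and enrolment by PRC are not given, so every value for them below is an assumption.

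**1. Two kinds of PRC.** Let R be the ratio of contact rates between high- and low-contact PRCs, pE and pN the shares of enrolled and nonparticipating clients under high-contact PRCs, and T the true ratio within PRC. Then

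pooled ratio = T × (pE·R + 1 − pE) / (pN·R + 1 − pN).

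| R | pE | pN | T | Pooled ratio |
|---|---|---|---|---|
| 2 | 0.70 | 0.40 | 1.00 | 1.70/1.40 = 1.21 |
| 3 | 0.60 | 0.40 | 1.00 | 2.20/1.80 = 1.22 |
| 1.5 | 0.70 | 0.40 | 1.00 | 1.35/1.20 = 1.125 |
| 2 | 0.50 | 0.40 | 1.00 | 1.50/1.40 = 1.07 |
| 2 | 0.40 | 0.70 | 1.20 | 1.2 × 1.40/1.70 = 0.99 |
| 3 | 0.40 | 0.60 | 1.20 | 1.2 × 1.80/2.20 = 0.98 |

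With equal mix or R = 1 there is no distortion.

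**2. How large R must be.** Setting the pooled ratio to 1.20 with T = 1 gives R = (0.2 + d)/d, where d = pE − 1.2·pN.

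- 70% vs 40%: d = 0.22, R = 0.42/0.22 = 1.91.
- 60% vs 40%: d = 0.12, R = 0.32/0.12 = 2.67.
- 50% vs 40%: d = 0.02, R = 0.22/0.02 = 11.

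A moderate imbalance therefore needs about a twofold rate difference. A 10-point imbalance would need an implausible one.

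**3. A case with two PRCs.** PRC A makes 8 contacts per client-month and enrols 6 of 20 clients; PRC B makes 2 and enrols 1 of 20. Enrolled: (6×8 + 1×2)/7 = 50/7 = 7.14. Not enrolled: (14×8 + 19×2)/33 = 150/33 = 4.55. The ratio is 1.57, while it is 1.00 within each PRC. These inputs are deliberately strong.

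**4. What stratifying by PRC achieves.** Simulations with 15 PRCs, 40 enrolled clients spread unevenly, no app effect, and PRC contact rates varying with coefficient of variation CV:

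- *Poisson counts* (caseload 20, mean 12 contacts): the pooled ratio reaches 1.20 in 1–3% of runs at CV 0.25, 6–11% at CV 0.5 and 16–20% at CV 1.0. The Mantel-Haenszel ratio stratified by PRC does so in at most 0.1%.
- *Overdispersed counts* (200 comparators, mean 24, negative-binomial dispersion 1 within PRC): pooled against stratified is 15% vs 18% at CV 0, 20% vs 19% at CV 0.5 and 26% vs 22% at CV 1.0.

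Stratification removes the shift due to PRC mix. It does not remove chance variation between clients, which dominates when clients within a PRC differ widely.

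**5. Precision.** With the second set of inputs, ignoring PRC variation, SE(log ratio) = √[(1/24 + 1)/40 + (1/24 + 1)/200] = 0.177. An observed 1.20 has a 95% interval of 1.20 × exp(±1.96 × 0.177) = 0.85 to 1.70.

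**The case against.** Several objections have force.

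- **The sentence on aggregation covers the whole section and may partly concern confidentiality.** The Ethical Considerations section says that shared findings will be deidentified or aggregated. This reading is possible. Even so, the comparison as stated is between two groups of clients, and no analysis within PRC appears anywhere.
- **This is a descriptive feasibility pilot, and model details may sit in a fuller plan.** That is fair for the choice of model or variance. The article itself, however, states the comparison and the threshold for a primary outcome.
- **The size is assumed.** This stands. A small imbalance or a small rate difference would not reach 20%.
- **Stratifying gains little if counts are strongly overdispersed.** This also stands for chance passes, as step 4 shows. It is a reason to report an interval, not a reason to leave the mix uncontrolled.
- **PRC is not a clean stratum.** A client may have more than one PRC, and may be reassigned if a PRC withdraws. The fix must deal with this.

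A reader might also infer that the PRCs have very different roles with known differences in contact pattern. The article shows different settings and types, but the Setting section also describes a common function, and no contact rates are given. A reader might infer that naming number and rate gives two chances to pass. The text names one target and does not say that either metric would suffice; what it leaves open is which one decides.

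**Conclusion.** The point holds as a statement about what the pooled comparison can do. PRC mix can carry the ratio past 1.20 with no app effect (1.21 with R = 2 and 70% vs 40%), or bring a true 1.20 down to about 1 (0.99 with the mix reversed). It rests on two assumptions that the article neither supports with figures nor rules out: that contact rates differ between PRCs by roughly twofold or more, and that enrolled and nonparticipating clients differ in PRC mix by some 20 to 30 percentage points. The actual size and direction are unknown. It would go too far to say that the pilot's ratio will be wrong, or that stratification would make false passes rare; the latter is true only if clients within a PRC vary little.

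That total number is not a comparable metric follows from the design and needs no assumed contact rates.

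**What to change.** Amend the Statistical Analysis Plan section before the pilot contact data are analysed:

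1. Name contacts per client-month as the metric that decides the 20% target. Totals may be shown as description.
2. Restrict comparators to nonparticipating clients of enrolled PRCs.
3. Assign each client one primary PRC, at enrolment for participants and at program entry for comparators, and keep that assignment if PRCs are added or changed.
4. Judge the target on a Mantel-Haenszel rate ratio stratified by primary PRC, and report it next to the crude ratio.
5. Give a 95% interval that allows for overdispersion between clients and for the small number of PRCs. A standard PRC-clustered interval is fragile with at most 15 PRCs. Show the interval beside the Go/No-Go statement.
6. State that this removes confounding between PRCs only. Selection of clients by their own PRC remains. So does the pilot rule excluding clients with more than 6 months in the program, unless comparators are limited in the same way.

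The cost is a few paragraphs of wording, a rule for the primary PRC, and a deidentified PRC code and observation time on each client's count. The client management system already attaches coaches to clients and is deployed across the PRC team, so the link should be obtainable. The interval will be wide, and the Go/No-Go text should say so.

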## Methods

### Feasibility Objectives and Outcome Measures

This work constitutes the first phase (R21; 2 years) of a 5-year federal research grant from the Agency for Healthcare Research and Quality (AHRQ) to test Peer PLUS, develop an implementation tool kit, and determine whether the tool has sufficient usability and impact to move to the final phase of the grant (R33; randomized clinical trial). The study aims and associated objectives and outcome measures for the present phase are summarized in Table 2.

To accomplish these objectives, in year 1, we will conduct a series of UCD activities, refine the platform, and deploy it with a small sample during beta testing. In year 2, we will continue UCD work, complete further refinement, develop an implementation tool kit, and conduct a pilot study.

For aim 1, we will use UCD methods to refine the functionality of Peer PLUS (eg, develop new features) and apply implementation science frameworks to develop an implementation tool kit. We will validate usability with the 10-item System Usability Scale (SUS) [44] and our own custom user experience survey incorporating RE-AIM elements. We will also measure frequency of use through app interaction logs as a proxy to determine likelihood of sustained use in the proposed R33 phase. Primary outcome measures for the pilot study will include usability ratings (SUS score ≥68; ie, above average) and app usage statistics (20% more connections to clients using the app, compared to contacts with nonparticipating clients, which is documented as standard of care). Based on the client population of the health system, we will target 25% as the proportion of clients approached who are eligible and consent to determine the feasibility of recruiting the target sample size (n=200) for the trial proposed in the R33 phase.

In aim 2, we will assess the platform’s impact on clients through several validated instruments, including the Substance Use Recovery Evaluator (SURE) [45] to assess recovery, the Consumer Assessment of Healthcare Providers and Systems (CAHPS) Experience of Care and Health Outcomes (ECHO) [48] to assess experience with receiving PRC services, and the WAI-SR [46,47] to assess therapeutic alliance. This will demonstrate the ability to robustly evaluate the app in the proposed R33 trial.

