Textbox 1.Study activities defined.Ethnography involves direct observation of users in their natural environment. We will use prelaunch and post-beta test and pilot ethnography to observe workflows and identify breakdowns and opportunities for technology refinement. [49]Stakeholder engagement includes focus groups or interviews using semistructured prompts modeled from RE-AIM (Reach, Effectiveness, Adoption, Implementation, and Maintenance) constructs and/or from ethnographic findings. We will use a variety of user-centered design strategies to engage end users to ascertain preferences, experiences, and priorities for using Peer PLUS (People Leveraging Urgent Support), including barriers and facilitators. Findings will inform updates to the platform and implementation tool kit.Surveys will be used to capture various measures of usability, user experience, and impact on recovery, client-PRC (peer recovery coach) alliance, and health outcomes, as well as participant demographics, and are detailed in Textbox 2.Semistructured interviews will focus on 2 critical components for predicting adoption of new technologies: perceived usefulness and relative advantage. [50] As our PRCs already use technology for both communication and tracking, the perceived usefulness and relative advantage of Peer PLUS for each of these uses will be explored.PRC client tracking sheet is a spreadsheet currently used by PRCs to track certain client data as part of standard practice. We will leverage this to gather demographic data related to this overall client population and characterize nonparticipating clients.Peer PLUS use log data will be collected automatically by the app. Data points include (1) user-specific logins, (2) number and type of messages sent (eg, standard, appointment, and referral), (3) number of resources viewed and uploaded, (4) number of calendar appointments added, (5) number of client profile edits, (6) time elapsed between message received and read, and (7) time elapsed between notification sent and app opened. We will not collect message content, names, or other personal identifiers; data stored and analyzed will use participant ID numbers, and dates will be represented as time elapsed since study initiation.Implementation tool kit development includes definitions, policies, and procedures for both setup and usage of the platform. This will be developed iteratively throughout the study using findings from all phases.

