## Results

Prelaunch ethnography was conducted in 2023 and included workflow observations of 3 PRCs. Notable findings related to the significant need for integration and organization of paper-based resource documents into a centralized digital platform, as well as the opportunity for reducing the unnecessarily complicated nature of the existing workflow due to its multiple siloed sources of information and varied communication modalities. Additionally, the lack of documentation with respect to PRC tasks completed was noted. These observations, along with subsequent co-design sessions, informed the design of the Peer PLUS app, which was ultimately deployed in the initial beta test, along with the initial version of the implementation tool kit.

Our planned iterative design work continued through 2024 and 2025 with the completion of 3 beta tests in the field and a formal heuristic evaluation of the Peer PLUS platform (mobile app and client management system). A total of 3 PRCs and 7 clients were enrolled across the 3 beta tests. The first included 2 PRCs and 4 clients. In the second, we elected to focus on the client management system, enrolling the 2 PRCs from the first test along with 1 additional PRC. The third test included these 3 PRCs and 6 clients, 3 of whom had participated in the prior test. Beta testing culminated in a refined HIPAA-compliant minimal viable product that will be evaluated in the planned pilot study, for which recruitment began in late 2025. The beta tests allowed us to expand and refine the design, including allowing for more complex case management (more than 1 PRC attached to a client), integrating functionality between the online and mobile apps (sending messages, sharing resources, and creating appointments), and providing a way to create customized data snapshots for reporting (tracking grants associated with each PRC). Throughout the co-design work with PRCs, we found the client management system covered a wide gap in technology-supported documentation of client engagement. Thus, we have deployed the client management system broadly across the entire PRC team as part of standard care and will be deriving learnings from a separate program evaluation component of this project.

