This project was proposed due to the limited understanding of the impact of technology-facilitated communication between PRCs and their clients. The unique role of the PRC as nonclinical staff who provide support to clients in a manner that is both formal (ie, as employees of a health system, with a need to document and track various data for operational and reporting purposes in a manner that is compliant with legal regulations and company policies) and informal (ie, as peers, with communication often occurring through personal devices) presents many challenges to both communication and documenting client engagements. Prior to study initiation, our health system’s PRCs relied on face-to-face meetings, text messaging, paper mail, and voice calls to communicate with hundreds of existing and potential clients per month, a system that is inefficient and limits topics of discussion due to privacy and security concerns. Moreover, tracking these interactions was done manually, which is prone to errors and disrupts workflow, displacing time that could be spent engaging in meaningful client interaction. A system that offers secure communication that can be tracked with background analytics is a solution to this problem. As engagement with community resources and treatment providers is an additional goal of client support, a digital solution to track referrals and completion of activities will also help to elucidate the most used and helpful nodes in the ecosystem of support surrounding clients.

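### The primary 20% contact target sets no common source or unit of contact for the two groups, so it can be met or missed through differences in capture alone

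*Protocol article*

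**What the plan says.** All references are to the protocol article.

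- **The comparison.** Under Statistical Analysis Plan: "we will compare the number and rate of connections to clients using the platform to PRCs’ documentation of contact with nonparticipating clients". The purpose is "to determine whether the target of 20% more contacts with enrolled clients was met".
- **Its status.** Feasibility Objectives and Outcome Measures lists it as a primary pilot outcome, in the words "app usage statistics (20% more connections to clients using the app, compared to contacts with nonparticipating clients, which is documented as standard of care". It is a milestone in Table 2 and one of three feasibility targets in the Abstract. The Abstract makes the later trial phase conditional on the feasibility metrics, and Table 3 places a go/no-go decision in months 23 to 24.
- **What the app log holds.** Textbox 1 says the log is collected automatically. Its data points include "number and type of messages sent (eg, standard, appointment, and referral", along with logins, resources, calendar entries, profile edits and elapsed times. Calls, face-to-face meetings and encounter notes are not listed. In Table 4, the only contact-related data point for enrolled clients is platform use data from the application server.
- **What exists for other clients.** The Statistical Analysis Plan section refers only to PRCs' documentation. Textbox 1 describes the tracking spreadsheet: "PRC client tracking sheet is a spreadsheet currently used by PRCs to track certain client data as part of standard practice". The Results section reports a later change: "we have deployed the client management system broadly across the entire PRC team as part of standard care". Table 1 shows that encounter notes are entered in that system.

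**The concern.** The two sides of the ratio appear to come from different instruments with different units. A message sent through the app is counted without anyone acting. A text, call or visit with a nonparticipating client counts only if the PRC enters it, and one entry may stand for a whole exchange. Conversely, the app is meant for asynchronous communication outside in-person meetings, so a log-based count would leave out calls and visits with enrolled clients. The article defines neither a connection nor a contact, and does not say that both groups are counted from the same place.

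PRCs already text their clients. Moving the same thread into the app changes how it is counted even if nothing about the contact changes. A pass could then reflect better capture, and a fail could hide a real increase. This figure feeds the decision to proceed to the randomized phase.

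**Working it through.** The 20% target is a threshold. The article gives no baseline contact rate, variance, alpha or power for it, so there is no stated calculation to reproduce. The check is how far the observed ratio can depart from the true one if the enrolled side is the app log and the other side is PRC entry.

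**Inputs**

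- Target ratio: 1.20 (Statistical Analysis Plan; Feasibility Objectives and Outcome Measures).
- *R*: true ratio of contacts per client, enrolled to nonparticipating.
- *s*: share of enrolled clients' contacts that pass through the app.
- *k*: log entries per contact, with a contact counted as a PRC would document it.
- *c*: completeness of PRC documentation for nonparticipating clients.

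The documents give no value for *R*, *s*, *k* or *c*. All values below are assumptions.

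**Formula:** observed ratio = *R* × *s* × *k* / *c*

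**Target met with no true difference (*R* = 1)**

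- With *s* = 1 and *k* = 1, the ratio is 1/*c*. It reaches 1.20 when *c* ≤ 1/1.20 = 0.833.
- *c* = 0.90 gives 1.11; 0.80 gives 1.25; 0.70 gives 1.43; 0.60 gives 1.67.
- With *s* = 1 and *c* = 1, the ratio is *k*. So 1.2 log entries per documented contact gives 1.20, and 2 gives 2.0.

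**Target missed despite a true increase (*k* = 1, *c* = 1)**

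- The ratio is *R* × *s*. With *R* = 1.5 and *s* = 0.6 it reads 1.5 × 0.6 = 0.90.
- The share needed to reach 1.20 is *s* ≥ 1.20/*R*: 0.92 for *R* = 1.3, 0.80 for *R* = 1.5, and 0.60 for *R* = 2.0.

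**Combined range.** With *s* from 0.3 to 1, *k* from 1 to 3 and *c* from 0.6 to 1, a true ratio of 1.0 can read anywhere from 1 × 0.3 × 1/1 = 0.30 to 1 × 1 × 3/0.6 = 5.0.

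**With one source, all channels and one unit.** Here *s* = 1 and *k* = 1, and the observed ratio is *R* × (completeness for enrolled / completeness for nonparticipating). If completeness is equal, the ratio equals *R*: a true 1.0 reads 1.00 and a true 1.2 reads 1.20. Equal completeness still matters. An assumed 0.90 against 0.75 would give 0.90/0.75 = 1.20 with no true difference.

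**The case against.** The strongest reply is that the Statistical Analysis Plan section never says the enrolled count comes from the log. It gives the log its own sentence and purpose, a categorical analysis of engagement, and then describes the contact outcome without naming a source for the enrolled side. The phrase about clients using the platform may only identify which clients are meant, and the Table 2 milestone can be read that way. The platform also includes the client management system, so both sides could already come from there. This stands in part: the log source is an inference. It rests on the outcome being classed among app usage figures and on Table 4 offering no other contact-related source for enrolled clients. It is the natural reading, but not a stated one.

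Four stronger readings are tempting, and the documents do not support them.

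- **That the tracking spreadsheet is the source of the comparator counts.** Textbox 1 names it for demographics and for characterizing nonparticipants, and Table 4 gives race, ethnicity and age group as examples. No section assigns contact counts to it.
- **That PRC documentation in the pilot is known to be incomplete.** The remark that "tracking these interactions was done manually, which is prone to errors and disrupts workflow" describes practice before the study. The gap reported in Results comes from the prelaunch ethnography and concerns PRC tasks. The client management system has since been deployed and may have improved matters, although entry still depends on the PRC.
- **That the ratio is biased upward.** Off-app contacts missing from the log act in the opposite direction, and the net effect cannot be determined.
- **That comparing numbers is itself an error.** A rate is planned alongside, and reporting counts as description is ordinary.

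It can also be said that a condensed article leaves units and denominators to a fuller plan. That does not dispose of the point. The article itself describes a comparison with different terms and apparently different capture on its two sides, for a primary go/no-go measure.

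**Conclusion.** The point holds as a defect in how the primary contact outcome is described. One side is connections to app users, most naturally automatic log counts; the other is PRC-entered documentation; no common source or unit is set. The ratio can therefore be met or missed through capture alone. For scale, with no true difference and a log that records each contact once, documentation that is 83.3% complete or less is enough to reach 1.20. In the other direction, a true ratio of 1.5 reads 0.90 if 60% of enrolled contacts go through the app and documentation is complete.

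These figures rest on assumed capture rates and on the inferred log source. They show that the target is sensitive to capture. They do not show that it will be wrongly met or wrongly missed. If the investigators already intend to count both groups from the client management system, the remedy is to say so and to fix the unit.

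**What to change.** 1. **One source.** Take contacts for both groups from the encounter records of the client management system, which the whole PRC team now uses, and name it as the source for this outcome.
2. **One unit, all channels.** Count app messages, texts, calls, mail and in-person meetings under a single prespecified definition of a contact. Client-days with at least one contact is one option; it ignores repeat contacts within a day, and other units are defensible.
3. **One instruction.** Give PRCs the same documentation rule for enrolled and nonparticipating clients, so that completeness is as equal as possible.
4. **One criterion.** Judge the 20% target on the ratio of rates per client-month. Keep raw numbers as description only.
5. **Logs apart.** Report app-log messages as a separate engagement measure that does not enter the ratio.
6. **Name the contrast.** State that the comparison is the mobile app added to a client management system used for everyone.

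The cost is a change of protocol and analysis wording and a report from an existing system. PRCs must also record app conversations as encounters, which is extra entry work, and the ratio may look less favourable. Both sides will still depend on PRC entry, so the fix removes the built-in difference in capture but does not guarantee complete capture.
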